**Administrative Responsibilities**

**Study Resources:** At the University of Utah, resources include a clinic room in Primary Children’s Medical Center that is restricted to use for the research of [name] and equipped with EMG equipment for MUNE and C-MAP assessments, as well as standard medical equipment (to check blood pressure, etc.); access to physical therapy and pulmonary function testing. DEXAs are performed at University Hospital; offices with computers are located in the School of Medicine; lab space is located at the SOM and at the Eccles Institute of Human Genetics, where protein studies are accomplished. We also use the GCRC for DNA extraction and send blood samples to other study sites for mRNA analysis (Montreal) and SMN copy-number (Ohio State). A Freezer maintaining -80 degrees centigrade is located in the SOM lab and houses our DNA. Qualified personnel at Utah include the PI, Clinical Trials Manager [name]; study coordinators; research dietician; research nurse; physical therapist; PFT and DEXA technicians; and informatics and nursing staff at the University of Utah General Clinical Research Center (GCRC).

**Recruitment:** We propose to recruit patients primarily from the Indiana SMA Patient Registry. When the registry receives information from an interested and eligible SMA patient, they will forward it to the study site geographically closest to the patient. Each study site will then contact the family to begin screening and enrollment procedures. This study will also advertise to interested clinicians in the journal Neurology, and directly to families on the Project Cure SMA and Families of SMA web sites. A toll free number will be established for the sole purpose of referring interested physicians and families to the nearest study site. This toll free number will be for informational purposes only and no identifying information will be collected.

**Control of Investigational Devices/Drugs:** VPA is an investigational drug insofar as it has not yet been approved for use in SMA patients. Its use is controlled by the study pharmacist at the Central Pharmacy of Primary Children’s Medical Center. She stores and dispenses VPA, Carnitine, and placeboes, mailing study drugs out under the labels of “Study Drug A” and “Study Drug B” to the parents of our pediatric subjects. Study drugs are mailed at specific times in the study to ensure proper use: after enrollment is approved, and every three months thereafter. Safety labs are required 2 weeks after start of drug/placebo and 2 weeks after all participants go on drug; safety labs are also done every 3 months, either at the time of a study visit or at a lab local to the families’ residences. The PI approves the calculation by weight of subject of the proper dosing.

**Communication Plans for Multi-Center Studies:** The investigator and coordinator(s) at each study site will be responsible for enrolling and evaluating study patients and collecting all study information. Patient samples and other patient information are given an identifying number and the code key is kept in a password protected computer. Patient files are stored according to number and are kept in locked files by the investigators. A central medical monitor will monitor laboratory values and adjust medication dosage for all sites as needed. Adverse events will be reported by investigators and coordinators at each site and will be reviewed by a data and safety monitoring board. Distribution of all medication is performed by a pharmacist at Primary Children’s Medical Center.

The GCRC Informatics Core will serve as the infrastructure for a data coordinating center (DCC). The GCRC Informatics Core will be responsible for applying the best practices of data management, study design, safety reporting and clinical trial conduct to clinical research protocols. It will also provide project direction and management, data security and other necessary support from existing resources within the GCRC Informatics Core. There will be additional staff required for this project, a part time Database Administrator (DBA) and a full time clinical coordinator. Each study center will have complete access to its own patient population date that is centrally stored at Utah. Study populations and their resulting data are combined to create a large enough sample for clinical and statistical significance. Interim results, which are already deidentified, will be compiled by the GCRC informatics director and shared with co-investigators and collaborators as the data pertains to their own specialties.

Regular conference calls including *all* multi-center staff (PIs, coordinators, data manager, physical therapists, etc.) allow for discussion of problems, possible changes to protocol, plans for interim data collection, analysis, and publication. Each conference call is summarized in minutes and distributed to all multi-center staff.

**Participating Sites outside the University of Utah:** The other five sites involved in the multi-center study are located at the Children’s Hospital of Michigan at Wayne State University; Johns Hopkins Hospital and Johns Hopkins University; University of Wisconsin Medical School, Ohio State University, and Centre de Recherche de l'Hôpital Sainte-Justine in Montreal, Canada. Each of the site PIs are named co-investigators of this study. All participating sites maintain IRB approval and are equipped to handle safety concerns as they may arise. Safety of information is handled as described above: participants’ private health information is deidentifed before being sent to the central data site at Utah and then kept in locked cabinets. Participants’ health safety is protected in numerous ways: reactions to the study drug through regular lab draws, oversight of labs by the Central Lab coordinator, an unblinded study coordinator, and the Medical Monitor; reporting of Adverse Events as stipulated by the IRBs and medical follow-up as needed; and overnight care at the different university’s GCRCs or equivalent.

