We hypothesize that treatment with VPA increases expression of SMN protein via up-regulation of SMN2 gene expression, resulting in the rescue of motor neurons and allowing re-innervation. Preliminary safety data from a pilot clinical trial at the University of Utah site demonstrates that giving valproic acid without carnitine supplementation is likely to deplete carnitine in a high percentage of SMA patients over the proposed study period, potentially increasing toxicity and resulting in reduced strength and function, thus confounding results of a clinical therapeutic trial. Thus, the trial design takes this into account by examining the use of these two compounds together. A variety of outcome measures will be used to evaluate efficacy of these drugs, including: Blood Chemistries (CBC with platelets, AST, ALT, amylase, lipase, carnitine profile, basic metabolic panel, and valproic acid level); Functional Status/Strength as assessed via Modified Hammersmith Functional Motor Scale (MHFMS) and the Project Cure Functional Motor Scale, Myometry, Pulmonary Function Testing, Quantitative assessment of SMN mRNA from blood samples, Peds QL™ assessment, Max CMAP amplitude/area and Ulnar MUNE (Modified Motor Unit Number Estimation),Growth and vital sign parameters, 3-Day Dietary Record, and Dual Energy X-ray Absorptiometry (DEXA) scanning as a measure of changes in lean muscle mass over time, and investigation of genetic mechanisms which influence the severity of phenotype.

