**Study procedures**

All study patients from both cohorts will complete two baseline screening visits approximately one month apart. Upon completion of these baseline visits, patients will be divided into treatment arms and be given study medication. Patients in cohort 1 (SMA “sitters”) will be randomized to participate in either the treatment arm (group 1) or the placebo arm (group 2). Patients and investigators will remain blinded for the first six months of the study. After six months, patients in the treatment arm (group 1) will continue on study medication for an additional 6 months. All children enrolled in the placebo arm (group 2) will be switched to study medication and continue on treatment for six months. Thus, half the children will receive treatment for a full 12 months, while the other half will receive treatment for the last 6 months of the study. Patients in cohort 2 (SMA “standers and walkers”) will receive treatment for the entire 12 month time period.

Safety Labs will be drawn 2 – 4 weeks after screening visit 2 to assess safety labs and valproic acid and carnitine levels. This can be done via their local laboratories and the results would be faxed to the central study site. Any dosing adjustments needed will be coordinated through the medical monitor to keep investigators blinded until completion of the study. Additional safety labs for cohort 1 will be drawn 2-4 weeks after Screen 2, 6.5-7 months and 9 months. Additional safety labs for Cohort 2 will be drawn 2-4 weeks after Screen 2. Safety labs do not require a visit to the study site, but may be coordinated through patient’s local pediatrician.

**Cohort 1**: SMA “sitters”: 2 – 8 yrs

|  | Screen 1 | Screen 2 | Safety Lab 1 | Visit 1 | Visit 2 | Safety  Lab 2 | Safety Lab 3 | Visit 3 |
| --- | --- | --- | --- | --- | --- | --- | --- | --- |
|  | T-1 mo | T=0 | .5-1 mos | 3 mos | 6 mos | 6.5-7 mos | 9 mos | 12 mos |
| GROUP 1:  30 subjects | Baseline | Baseline  Start Drugs | VPA+ C | VPA+ C | VPA+C | VPA+C | VPA+C | VPA+C |
| GROUP 2:  30 subjects | Baseline | Baseline | Placebo x2 | Placebo x2 | Placebo x2 | VPA+C | VPA+C | VPA+C |

**Cohort 2:** SMA “standers and walkers”, ages 3 – 17 yrs

|  | Screen 1 | Screen 2 | Safety Lab 1 | Visit 1 | Visit 2 | Safety Lab 2 | Safety Lab 3 | Visit 3 |
| --- | --- | --- | --- | --- | --- | --- | --- | --- |
|  | T-1 mo | T=0 | .5-1 mos | 3 mos | 6 mos | 6.5-7 mos | 9 mos | 12 mos |

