
Blood samples will be obtained either immediately before or after the nerve conduction testing. If the patient is going to be sedated, the blood draw will be done while the patient is still under sedation. Three to six milliliters of blood is needed at each visit to check for safety monitoring and drug levels. If patients elect to have their DNA collected for genetic studies, an additional five to ten milliliters will be collected during the course of the study. If a DEXA scan is to be completed during this visit, it will occur either immediately before or immediately after the MUNE procedure. The total time of testing on the first day, including all of the testing above, is approximately 2 hours.

Prior to the patient’s arrival for each study visit they will be given a 3 day dietary/supplement record, which they will asked to complete and bring with them. This information will be reviewed with them by a dietician either on their arrival or on the first day of testing. If patients forget to bring their completed dietary record, they will be asked to complete it the following week and return it promptly. The site coordinator will administer the parent questionnaire of the quality of life tool (PedQLTM), which must be filled out by the same parent at each visit. Total time to complete the questionnaires is about 15 minutes.

Clinical testing on the second day includes the following: A physical therapist will perform a functional assessment using either the Modified Hammersmith Functional Motor Scale – SMA (cohort 1) and the Project Cure Functional Motor Scale for SMA (cohort 2). Functional testing will last between 15 to 30 minutes. Patients 5 years of age or older will receive pulmonary function testing and myometry testing. A physical therapist will perform myometry testing which uses a small device to help measure strength of patients’ hand grip and arm flexion and leg extension. A technician will perform pulmonary function testing which includes routine spiromerty, maximum inspiratory pressure (MIP) and maximum expiratory pressure (MEP). This testing will take approximately 30 minutes. Patients 5 years or older will complete the age appropriate questionnaire of the quality of life tool PedQLTM on this day.

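### Complete site access to centrally stored patient data makes no exception for valproic acid and carnitine levels, and is not reconciled with the Cohort 1 blind

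*Protocol*

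**What the plan says.** **Who must be blinded.** Cohort 1 is a double-blind randomised comparison. Study procedures says: "Patients and investigators will remain blinded for the first six months of the study". The next paragraph gives a different end point: "Any dosing adjustments needed will be coordinated through the medical monitor to keep investigators blinded until completion of the study".

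**What is measured.** Background and Introduction lists among the blood chemistries "carnitine profile, basic metabolic panel, and valproic acid level". Study procedures sets the first on-treatment sample: "Safety Labs will be drawn 2 – 4 weeks after screening visit 2 to assess safety labs and valproic acid and carnitine levels". It later adds: "Three to six milliliters of blood is needed at each visit to check for safety monitoring and drug levels". The schedule has blood draws at month 3 and month 6 as well.

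**Where results go.** Of the safety labs, Study procedures says: "This can be done via their local laboratories and the results would be faxed to the central study site". Data Safety and Monitoring has the medical monitor review all laboratory data, sign the case report form and return it to the Clinical Trials Manager.

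**Who can see the data.** Under Communication Plans for Multi-Center Studies: "Each study center will have complete access to its own patient population date that is centrally stored at Utah". The same heading says: "The investigator and coordinator(s) at each study site will be responsible for enrolling and evaluating study patients and collecting all study information". The paragraph on participating sites outside Utah places lab oversight with a Central Lab coordinator, an unblinded study coordinator and the medical monitor.

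**The concern.** The authors recognised that information driven by drug levels can break the blind, since they route dose adjustments through the medical monitor for that reason. They did not close the more direct route, which is the level itself. The access rule has no exception, and no sentence confines the levels to the unblinded roles.

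The primary outcome is the six-month change on the Modified Hammersmith scale (MHFMS), scored by a physical therapist in children aged 2 to 8 who must cooperate with testing. Encouragement, positioning and borderline scoring can all respond to knowledge of the arm. This is the trial's only randomised comparison, and no analysis can restore a blind that was lost while the scores were collected.

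**Working it through.** **Step 1. Does a level reveal the arm?** The Cohort 1 exclusion criteria bar current VPA or carnitine use, with a 12-week washout, and bar anticonvulsants. Study procedures titrates active drug to a VPA trough of 50-120 micrograms/ml. A measurable VPA level therefore points to active treatment. An absent level points to placebo, or to a child on active drug who is not taking it. For practical purposes the arm is shown.

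**Step 2. When is it available?** Two samples precede the month 6 visit: Safety Lab 1 (month 0.5 to 1) and Visit 1 (month 3). Both apply to the two Cohort 1 arms, 30 + 30 = 60 children.

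**Step 3. Do the rules fit together?**

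| Topic | What the protocol provides | Effect on the blind |
| --- | --- | --- |
| Dose changes | Go through the medical monitor | Protects |
| Lab oversight | Named roles, one expressly unblinded | Protects only if others are excluded, which is not stated |
| Local results | Faxed to the central study site, no recipient role named | Open: Utah has its own investigator, coordinators and physical therapist (Study Resources) |
| Stored data | Complete access for each centre to its own patients | Open: no exception for levels |
| End of blinding | First six months in one sentence, study completion in another | Undefined |

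The last three rows are not reconciled with the blinding requirement.

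**Step 4. What rests on inference?** That the site-accessible database holds the levels is not stated. It follows from their being listed study measurements and from lab review passing through the case report form. Access is granted to the centre without naming roles.

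**Step 5. How sensitive is the primary test to a scoring bias?** Inputs from the Sample Size section: SD 3.19, meaningful change 3 points, 25 completers (read as per arm), two-sided 5% test.

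- The plan's own figure: effect size 3 / 3.19 = 0.940 (stated as 0.941). The exact two-sample t-test with 25 per arm gives 90.3% power, which agrees with the stated 90%.
- Standard error of the difference: 3.19 × √(2/25) = 0.902; degrees of freedom 2 × 25 − 2 = 48.
- For an inert drug and a bias of b points between arms, the noncentrality is b / 0.902, and the false-positive rate is the two-sided rejection probability of the noncentral t on 48 degrees of freedom.

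| Assumed bias b (points) | b / 0.902 | Rejection rate |
| --- | --- | --- |
| 0 | 0 | 5.0% |
| 0.5 | 0.554 | 8.4% |
| 1.0 | 1.109 | 19.2% |
| 1.5 | 1.663 | 37.1% |

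The values of b are assumptions; the protocol offers no figure for them. For scale, 1.0 point is one third of the 3-point effect the trial is sized for.

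**The case against.** The strongest reply is that the protocol plainly intends to protect the blind. Safety-lab results go to the centre and not to the enrolling site, a central medical monitor handles laboratory values for all sites, and an unblinded coordinator exists, presumably so that revealing information can be kept apart. On this view the access sentence is a general data-sharing statement that yields to the specific blinding rule, and field-level permissions belong in data-management documents not shown here.

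Part of this stands. The intention is clear, and the access sentence can be read as carrying an unstated exception. But overseeing labs does not restrict who else sees them, and a rule that grants complete access is a poor basis for permissions that must withhold the one field that reveals the arm. The reply also does not cover Utah, which is both the fax destination and an evaluating site.

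Two stronger readings should be resisted. A reader might infer that the therapists who score the scale can look up each child's arm; nothing says that they have or use database access. A reader might also infer that the pediatrician or family receives the levels. The protocol lets the local pediatrician help arrange the safety labs, but the only recipient of results it names is the central study site.

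**Conclusion.** The point holds as an unreconciled conflict. The access rule and the fax route, as written, permit site staff who must be blinded to see results that reveal the Cohort 1 arm before the month 6 score. It is not shown that any rater would see them, so it should not be reported as a breach or as a certainty that all 60 allocations are exposed.

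The conclusion rests on one inference, that the levels are held in the data the sites can reach. The rejection rates of about 8%, 19% and 37% show how sensitive the primary test is to a bias of 0.5, 1.0 or 1.5 points averaged over all sites and raters. They do not estimate the effect of this sentence. The case for a change is that it protects the only randomised comparison at very little cost.

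**What to change.** 1. **Communication Plans for Multi-Center Studies.** Replace the access rule with wording such as: *each centre has complete access to its own patients' data except Cohort 1 valproic acid levels and carnitine profiles, which are masked from site investigators, site coordinators and MHFMS raters, including those at Utah, at least until all Cohort 1 month 6 scores are locked.*
2. **Study procedures.** Direct Cohort 1 level results only to the lab-oversight roles already named: the Central Lab coordinator, the unblinded study coordinator and the medical monitor. Any lab form returned to blinded staff should omit the levels. Other safety results continue as now.
3. **Study procedures.** Reconcile the two blinding periods, the first six months and until study completion, so that the end of masking is defined.

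The cost is a field-level restriction in the existing database and a changed reporting address for the level results. The roles already exist and the medical monitor still sees every level. The small downside is that a site needing a level must ask the medical monitor for it.
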